## Abstract

**Background:**

There is no recommendation to screen ferritin level in blood donors, even though several studies have noted the high prevalence of iron deficiency after blood donation, particularly among menstruating females. Furthermore, some clinical trials have shown that non-anaemic women with unexplained fatigue may benefit from iron supplementation. Our objective is to determine the clinical effect of iron supplementation on fatigue in female blood donors without anaemia, but with a mean serum ferritin ≤ 30 ng/ml.

**Methods/Design:**

In a double blind randomised controlled trial, we will measure blood count and ferritin level of women under age 50 yr, who donate blood to the University Hospital of Lausanne Blood Transfusion Department, at the time of the donation and after 1 week. One hundred and forty donors with a ferritin level ≤ 30 ng/ml and haemoglobin level ≥ 120 g/l (non-anaemic) a week after the donation will be included in the study and randomised. A one-month course of oral ferrous sulphate (80 mg/day of elemental iron) will be introduced vs. placebo. Self-reported fatigue will be measured using a visual analogue scale. Secondary outcomes are: score of fatigue (Fatigue Severity Scale), maximal aerobic power (Chester Step Test), quality of life (SF-12), and mood disorders (Prime-MD). Haemoglobin and ferritin concentration will be monitored before and after the intervention.

**Discussion:**

Iron deficiency is a potential problem for all blood donors, especially menstruating women. To our knowledge, no other intervention study has yet evaluated the impact of iron supplementation on subjective symptoms after a blood donation.

**Trial registration:**

NCT00689793

## Background

Clinical trials have shown that non-anaemic women with unexplained fatigue may benefit from iron supplementation [1-5]. A one-month ferrous sulphate treatment showed positive effects on fatigue in women with a mean serum ferritin of 30 ng/ml [5]. Improved aerobic capacity, assessed by VO_2max_, has also been associated with iron supplementation in women with non-anaemia iron deficiency [6].

The haemoglobin content of a whole-blood donation (450 ml) is around 55 g to 70 g, and the iron content is around 187 mg to 283 mg. This iron amount corresponds to a range of 66% to 97% of the total stored iron in an average menstruating woman. According European Council directives, it is not mandatory to measure the donor's ferritin level before a blood donation. However, to avoid iron deficiency anaemia induced by blood donations, women's haemoglobin level is controlled, and their blood donation frequencies are limited to three or four per year.

According to a recent survey, 11% of female and 4% of male blood donors complained from fatigue after a donation [7]. The greater proportion of haemoglobin, which is removed from women who are smaller in size and have higher prevalence of iron deficiency, can probably explain the gender difference. Moreover, fatigue is the third complication following a blood donation, after bruise and sore arm. This has an adverse impact on blood donations. Fatigue was associated with a 20% reduction in blood donor return rates at one year post donation [8].

Two recent trials have also shown that a short period of ferrous sulphate supplementation decreased the incidence of iron deficiency in blood donors [9,10]. Furthermore, it produced a rapid improvement in haemoglobin level between blood donations, which improved the fidelity of donors [10]. To our knowledge, no study has shown the impact of iron supplementation on female blood donors' symptoms, such as fatigue.

## Method/Design

### Objectives

Our primary objective is to test the hypothesis that a one-month iron supplementation (oral ferrous sulphate, 80 mg/day of elemental iron), after blood donation, has positive effects on symptoms of fatigue in women blood donors with a serum ferritin concentration ≤ 30 ng/ml, and no anaemia.

Secondary objectives are to assess the effect of treatment on aerobic capacity, mood, quality of life, and haematological parameters.

### Primary outcomes

We will assess changes in self-reported fatigue at one-month follow-up. The self-reported fatigue will be measured using a 10 cm visual analogue scale (VAS), which has demonstrated good psychometric properties in this context [11].

### Secondary outcomes

We will assess changes in fatigue, mood disorders, and quality of life [11-13], using a self-administered questionnaire; changes in maximal aerobic power (estimated by the Chester Step Test) [14]; changes in serum ferritin and haemoglobin; and adherence to treatment.

## Design

Our study will be a pragmatic randomised placebo controlled trial. Donors will join the study and sign an informed consent before blood donation. Approximately 450 ml of venous blood will be collected (not used for the study) within a blood pack set (NGR6449B, Fenwal, Belgium), which allow a predonation sampling of an excess 12 ml for further testing in our study. One week after, volunteers with a concentration of ferritin ≤ 30 ng/ml, and a concentration of haemoglobin ≥ 120 g/l, will be included in the study and randomised to receive either ferrous sulphate (80 mg/day of elemental iron) or placebo for four weeks (See Figure 1).

**Figure 1 F1:**
[figure not shown]
**flow chart**.

## Setting

This randomised controlled trial will take place at the University Hospital of Lausanne. The blood donation will take place in the Blood Transfusion Service, and the follow-up in the Department of Ambulatory Care and Community Medicine.

## Study participants

Study participants will be recruited among women coming spontaneously to the Blood Transfusion Service to donate blood. Donors aged 18 yr – 50 yr and eligible to donate blood, according to the blood donation eligibility guidelines of the Swiss Transfusion Service, will be considered for inclusion. Exclusion criteria are psychiatric conditions or diseases that render the participant unable to give consent; thyroid, hepatic, rheumatic, kidney, cardiopulmonary, or intestinal disease; acute or chronic inflammation, diabetes, hemochromatosis, pregnancy, and medical treatment that could perturb iron absorption.

## Randomisation, allocation and masking of the study

A physician working at the Blood Transfusion Service will be responsible for seeing all potential participants (i.e., female donors aged 18 yr – 50 yr) and will assign the next available study number. Once eligibility criteria for a blood donation is fulfilled and an informed consent is obtained, blood donation will be performed. The randomisation will take place a week after the blood donation with the following criteria for inclusion. Haemoglobin level ≥ 120 g/l, ferritin level ≤ 30 ng/ml. Randomisation will take place at an independent pharmacy, according to a pre-established computer-generated list using simple randomisation. Each drug package will be coded with a unique number according to the randomisation schedule. The codes will be held by the pharmacist and remained unbroken until the analyses are completed. A research assistant responsible for seeing the blood donors will allocate the next available treatment pack in a telephone call to the pharmacist. Patients, caregivers, and assessors will be blinded to treatment assignment until the end of the trial. Participants will remain on the same allocation throughout the study (intention-to-treat protocol). An electronic device that assesses adherence to treatment will also be delivered. The pills and electronic device will have the identical appearance for the experimental and placebo groups. The iron supplement and the placebo will have the same taste.

## Treatment

Volunteers will receive either 80 mg/day oral ferrous sulphate (Tardyferon, Robapharm, Boulogne, France) or placebo for four weeks. To decrease side effects, the pills will be taken during breakfast. Currently, oral ferrous sulphate is the reference treatment for iron deficiency without anaemia. Oral ferrous sulphate is resorbed mainly in the duodenum and proximal jejunum. Iron resorption depends directly on the level of hepcidin. Described side effects are upset stomach, constipation, diarrhoea, nausea, and black or dark-coloured stools. No serious complications have been reported. However, uncommon cases of allergic reactions have been described. Volunteers will be asked not to take over the counter vitamin or iron supplements.

## Measurements

Paramedical staff will collect data. Ten cm visual analogue scales, ranging from "no fatigue at all" to "very severe fatigue," associated with another self administered questionnaire focusing on fatigue (Fatigue Severity Scale, [11]) will be completed at randomisation (D0), and after the experimental phase (D28). The initial questionnaire has been translated into French and back translated for verification. The appropriateness and acceptability of the questions have been tested in our setting in pilot studies. For additional outcomes, depression and anxiety symptoms will be assessed using the Prime-MD questionnaire [13]. Health-related quality of life will be measured using the SF-12 questionnaire [12]. An evaluation of the amount of menstrual blood loss (Pictorial Bleeding Assessment Chart, [15]) will also be performed at baseline to detect any possible hypermenorrhea.

Complete blood count and ferritin concentration will be measured at D-7 (day minus 7), D0 and D28. C-reactive protein (CRP), an acute phase protein, will be analysed at D0 to identify volunteers whose ferritin concentration might be falsely elevated by occult infection or inflammation. Complete blood count will be measured using the Sysmex XE 2100 (Roche) haematology analyser. Ferritin and CRP will be measured by immunoturbidimetry.

To assess the change in aerobic capacity at baseline (D0) and after iron treatment (D28), a step test (Chester Step Test) will be carried out. Measurements obtained with this protocol have been demonstrated to give excellent test-retest reliability, and are highly correlated with VO_2max _(r = 0.92) [14].

Adherence to treatment will be measured by an electronic device, Medication Event Monitoring System (MEMS; Aardex Europe, Switzerland), which records the date and time that the pill container is opened [16]. Questions will be asked at D28 to evaluate whether the electronic monitoring was properly used (for example, if each opening is correlated with the consumption of one pill). Unused pills will also be counted. Adherence will be quantified by dividing the number of times the device was opened by the total number of days of observation. A study that used this system has shown that compliance and motivation to take the treatment were improved [17].

The success of blinding will also be evaluated in the questionnaire at D28. Serious adverse events will be reported to the principal investigator within 48 hr, and will be recorded in follow-up notes.

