## Statistical methods

### Sample size

The main outcome variable is the level of fatigue at one month. The sample size for randomised volunteers was calculated using a two-sample comparison of means to detect a one point difference between the groups on the visual analogue scale, similar to the minimal clinically appreciable difference for pain [18]. According to a previous study [5], we can expect a standard deviation of two points. For a two-tailed test (α = 0.05, power = 0.80), each group should include 63 participants. Anticipating a 10% dropout rate, the total sample size is rounded to 140 participants.

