### Statistical analysis

Analysis will be conducted on an intention-to-treat basis. The measure of effect is the change in fatigue level. The null hypothesis is that there will be no difference in fatigue VAS scores between the experimental and control groups at 28 days, adjusted for the baseline level of fatigue on the same scale. The significance level will be set at 5%, using a linear regression with the treatment group, and using the baseline values of fatigue as independent variables, and using fatigue levels at 28 days as the dependent variables. The measure of effect for the secondary outcomes will be assessed by the same method. If ferritin levels are not normally distributed, a transformation will be used. All calculations will be performed with StataCorp 2008, Statistical Software: Release 10.0, Stata Corporation, College Station, Texas.

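### Minor improvement for the secondary blood outcomes: use the pre-donation haemoglobin and ferritin values as a second covariate, and fix the ferritin scale in advance

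*Protocol article*

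**What the plan says.** All references are to the protocol article.

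- **Blood samples (Measurements).** "Complete blood count and ferritin concentration will be measured at D-7 (day minus 7), D0 and D28". The Design section says the D-7 sample is drawn before the donation. The randomisation section places allocation one week after it, once haemoglobin is known to be at least 120 g/l and ferritin at most 30 ng/ml.
- **Primary model (Statistical analysis).** Fatigue at 28 days is regressed on treatment group and baseline fatigue.
- **Secondary outcomes (same section).** "The measure of effect for the secondary outcomes will be assessed by the same method". These outcomes include changes in serum ferritin and haemoglobin. The section does not say which blood sample is the baseline. Measurements equates baseline with D0 for the step test, and fatigue is first recorded at D0, so D0 is the natural reading.
- **Ferritin scale (same section).** "If ferritin levels are not normally distributed, a transformation will be used". Neither the transformation nor the criterion for non-normality is named.
- **Sample size.** "For a two-tailed test (α = 0.05, power = 0.80), each group should include 63 participants", and "Anticipating a 10% dropout rate, the total sample size is rounded to 140 participants".

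**The concern.** There are two points, both about haemoglobin and ferritin as outcomes.

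**A collected covariate is not used.** The D0 value is taken a week after a donation of about 450 ml and is range-restricted by the entry limits. Restriction of range tends to weaken a predictor. The D-7 value precedes both the donation and allocation, so it is a legitimate covariate, and two noisy readings plausibly predict D28 better than one. No model in the article names it. At stake is some precision in the haematological comparisons.

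**The ferritin rule looks at the wrong quantity and leaves the effect measure open.** Linear regression makes its distributional assumption about residuals. Raw ferritin levels can look non-normal for reasons unrelated to model fit: D0 ferritin is cut off at 30 ng/ml by eligibility, and D28 ferritin, if the arms are pooled, mixes treated and untreated women. Depending on what is seen, the result would be a difference in ng/ml, a ratio, or something else. At stake is whether the reported ferritin effect is defined before the data are seen.

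**Working it through.** **1. The plan's own figure.** Inputs from the Sample size section: difference 1 point, SD 2 points, two-sided α 0.05, power 0.80.

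n per group = 2 × (1.960 + 0.842)² × 2² / 1² = 2 × 7.849 × 4 = 62.8, so 63. With 10% dropout, 126 / 0.90 = 140. Both stated figures reproduce. The calculation is an unadjusted comparison of two means that takes no credit for any covariate, so nothing below affects it.

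**2. Gain from adding D-7 to D0.** Let a be the correlation of D0 with D28, b that of D-7 with D28, and c that of D-7 with D0. The documents give none of these; all values are assumptions.

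- D0 only: residual variance = 1 − a².
- D0 and D-7: R² = (a² + b² − 2abc) / (1 − c²), residual variance = 1 − R².

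| a | b | c | R², D0 only | R², both | Residual-variance ratio | SE reduction |
|---|---|---|---|---|---|---|
| 0.6 | 0.42 | 0.7 | 0.360 | 0.360 | 1.00 | 0% |
| 0.6 | 0.5 | 0.7 | 0.360 | 0.373 | 0.98 | 1.0% |
| 0.6 | 0.6 | 0.7 | 0.360 | 0.424 | 0.90 | 5.1% |
| 0.5 | 0.5 | 0.5 | 0.250 | 0.333 | 0.889 | 5.7% |
| 0.7 | 0.7 | 0.7 | 0.490 | 0.576 | 0.830 | 8.9% |
| 0.9 | 0.9 | 0.9 | 0.810 | 0.853 | 0.776 | 11.9% |

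The first row is the nil case: b = a × c = 0.6 × 0.7 = 0.42, so D-7 says nothing about D28 beyond what D0 says. Worked: (0.36 + 0.1764 − 0.3528) / 0.51 = 0.36.

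The SE reduction is 1 − √ratio. With a = 0.6 and c = 0.7, the variance falls by 0% to about 10%. Under equal correlations of 0.5 to 0.9 the SE falls by 5.7% to 11.9%; the last figure is a 22% fall in variance.

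**3. Cost of the extra covariate.** With 126 women analysed, one more covariate multiplies the variance by about 1 + 1/120 = 1.008, or 0.8%. This offsets part of the 2% gain in the second row and leaves a trivial net loss in the first.

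**4. Does the ferritin rule look at the right thing?** 126 women were simulated with a correct raw-scale model, exactly normal residuals, and log-normal D0 ferritin truncated at 30 ng/ml (parameters assumed). A Shapiro test rejected normality of the D0 levels in about 88% of trials, against 5% for the residuals. Pooled D28 levels were rejected in 12% to 48% of trials when the treatment effect was large (2.5 to 3.3 residual SDs), and no more than nominally for smaller effects. A check on levels can therefore call for a transformation that the model does not need.

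**5. Does the rule lose power?** Assumptions: log-normal ferritin, 63 per group, baseline truncated at 30 ng/ml, correlation parameter 0.6, treatment effect 0.25 on the log scale, 2,000 trials per setting. The conditional rule was taken to mean log if a Shapiro test on D28 levels rejects, and raw otherwise.

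| Log SD | Power, raw | Power, log | Power, conditional rule |
|---|---|---|---|
| 0.4 | 0.98 | 0.99 | 0.99 |
| 0.6 | 0.74 | 0.81 | 0.81 |
| 0.8 | 0.48 | 0.59 | 0.59 |

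Type I error lay between 0.045 and 0.055 for all three analyses. Only staying on the raw scale cost power. The rule matched log here with log-normal data and log as the chosen transformation; the protocol names neither.

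**The case against.** The case against is substantial.

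- **Nothing is stated wrongly.** Each outcome is already adjusted for its own baseline. A second covariate for two laboratory outcomes is optional, and an article commonly leaves covariate lists to the full protocol or analysis plan. This stands, and it limits the first point to a suggested improvement. The ferritin rule differs in that it is stated, and in a form that leaves the effect measure open.
- **The gain is assumed.** This stands: a nil gain is possible and is shown in the working.
- **The rationale for D-7 is not clear-cut.** D-7 haemoglobin is also restricted, because women must be fit to donate. The Background section puts the iron removed at 66% to 97% of an average menstruating woman's stores, and nothing in the article shows untreated ferritin returning to its D-7 level by D28. This stands. The argument that survives is only that two readings may predict better than one.
- **The ferritin rule will probably trigger a transformation anyway, and the treatment codes stay sealed until the analyses are completed.** Sealing limits any choice of scale that favours one arm. It does not say in advance which effect will be reported.

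A reader might go further and infer that the planned analysis is unadjusted or invalid, that the primary result or the sample size suffers, or that the ferritin rule itself wastes power. The documents support none of these. The models are baseline-adjusted, fatigue is recorded only at D0 and D28 so there is no unused earlier fatigue reading, the 140 reproduces without covariates, and the rule matched the log analysis in simulation.

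**Conclusion.** The point holds as a minor, nearly costless improvement to the secondary haemoglobin and ferritin analyses.

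For the D-7 covariate, the effect runs from nothing to about a 10% fall in residual variance under the moderate correlations assumed, and to about 12% of the SE under high equal correlations, less about 0.8% of variance for the degree of freedom. The size rests wholly on assumed correlations and on reading baseline as D0. It should not be described as a proven gain.

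For ferritin, the weakness is in pre-specification: the rule judges levels where residuals matter, and it fixes the effect measure only after the data are seen. A loss of power or an inflated type I error is not shown. The trial's primary conclusion does not depend on either point.

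**What to change.** In the Statistical analysis section:

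1. State that the haemoglobin and ferritin models include treatment group and both the D-7 and the D0 value of the same variable as covariates.
2. Replace the conditional rule with a fixed one: ferritin is log-transformed by default, as outcome and as covariates, and the treatment effect is reported as the adjusted geometric mean ratio with its confidence interval.

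The cost is wording plus one degree of freedom in two secondary models. No extra samples, visits or participants are needed, and the primary fatigue model and the sample size stay as they are.

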## Statistical methods

### Sample size

The main outcome variable is the level of fatigue at one month. The sample size for randomised volunteers was calculated using a two-sample comparison of means to detect a one point difference between the groups on the visual analogue scale, similar to the minimal clinically appreciable difference for pain [18]. According to a previous study [5], we can expect a standard deviation of two points. For a two-tailed test (α = 0.05, power = 0.80), each group should include 63 participants. Anticipating a 10% dropout rate, the total sample size is rounded to 140 participants.

### Statistical analysis

Analysis will be conducted on an intention-to-treat basis. The measure of effect is the change in fatigue level. The null hypothesis is that there will be no difference in fatigue VAS scores between the experimental and control groups at 28 days, adjusted for the baseline level of fatigue on the same scale. The significance level will be set at 5%, using a linear regression with the treatment group, and using the baseline values of fatigue as independent variables, and using fatigue levels at 28 days as the dependent variables. The measure of effect for the secondary outcomes will be assessed by the same method. If ferritin levels are not normally distributed, a transformation will be used. All calculations will be performed with StataCorp 2008, Statistical Software: Release 10.0, Stata Corporation, College Station, Texas.

### Missing data and drop-outs

Missing data will be handled using multiple imputation. Reasons for dropping out will be compared between the placebo and the ferrous sulphate groups at a significant level of 0.05. In the intention-to-treat analysis, dropouts will be considered as missing data and analysis will use multiple imputation to interpret the results.

## Ethical aspects

The study was approved in July 2008 by the University of Lausanne Ethics Committee for clinical research. The main risk for participants is developing anaemia after the blood donation. The blood test a week after blood donation will permit diagnosis of this complication, and anaemic volunteers will be removed from the study before randomisation. In this case, a doctor from the Blood Transfusion Service will introduce a three-month ferrous sulphate treatment and inform the individual's general practitioner. Another type of risk that may be encountered by volunteers is due to side effects of the treatment. As documented above, side effects of ferrous sulphate are well documented and tolerated by a majority of treated patients. Finally, there is no risk of inducing an iron overload in volunteers because only donors with a ferritin level ≤ 30 ng/ml will receive the treatment.

